#### PREHAB

PREHAB participants will engage in an individualized, total-body exercise and PFMX program. The total-body exercise prescription will consist of 60 minutes of home-based, unsupervised exercise on 3–4 days per week. Each session will be individualized, based upon a baseline assessment and will include: a 5-minute warm-up, 25 minutes of aerobic exercise (40-60% of heart rate reserve; HRR), 25 minutes of resistance training (5 exercises targeting major muscle groups performed at an intensity of 8–12 repetitions maximum), and a 5-minute cool-down. Training intensity progression will occur when the participant can complete aerobic exercise with mild exertion and/or when the participant can complete 15 repetitions of a given resistance exercise. Participants will be provided with varying intensities of resistance bands, a stability ball, and an exercise mat. The PFMX prescription will begin with instructions on how to engage the pelvic floor delivered by the RC trained in PFMX. The PFMX prescription will include a gradual increase in repetitions from 60 per day during weeks 1–2, 120 per day during weeks 3–4, and 180 per day during week 5 to the surgical date. The total number of repetitions of the PFMX will be divided equally between the rhythmic contractions (contract and relax over one second) and the sustained contractions (contract and hold for up to 10 seconds). Participants will be instructed to contract with maximal effort during all PFMX repetitions. The PREHAB intervention will be supported with a manual (translated into French) and exercise videos created by the co-investigating team. The RC will communicate with the PREHAB participants weekly via phone or email to ensure program compliance, support appropriate progression, and address any barriers to exercise that may prevent ongoing participation.

#### Usual care

RP patients will receive preoperative information from a urology nurse educator about PFMX, mobilization and general timeframes for return to normal activities following RP. The UC group will receive the same PFMX prescription as the PREHAB intervention and will receive weekly communication from the RC regarding compliance with the PFMX prescription to provide an attentional-control.

### Outcome assessments

Self-report measures and physical fitness assessments will be conducted at: baseline (following RP booking, prior to beginning group assignment) approximately 4–8 weeks preoperatively, within 1 week prior to RP, and at 4, 12, and 26 weeks postoperatively. All self-reported measures are available in English and French.

Full-scale trial feasibility will be assessed by: 1) recruitment rate (and reasons for non-participation); 2) attrition rate; and 3) adherence and contamination (through a physical activity log completed by the RC during the weekly communication). Adherence to the exercise prescription for the PREHAB intervention and to the PFMX prescription for both groups will be analyzed by calculating the percentage of total physical activity volume prescribed (i.e. total number of repetitions completed/total number of repetitions prescribed).

Musculoskeletal fitness will be assessed by grip strength dynamometry and isometric strength for elbow flexion and extension by handheld dynamometry. Grip strength will be measured using a hand grip dynamometer (Sammons Preston, model Jamar, Bolingbrook, IL, USA) with the participant asked to complete two maximal effort squeezes per hand while standing and arm extended and abducted to 45 degrees [39]. Grip strength will be recorded to the nearest kilogram, with the maximum value per hand used for outcome assessment. Isometric strength for elbow flexion and extension will be measured using a handheld digital dynamometer (Hoggan Health Industries, model Microfet2, UT, USA) that is positioned on the underside (for flexion) or topside (for extension) a table. Participants will be seated with elbow flexed to 90 degrees, with the dynamometer in hand, either on the under or topside of table and will gradually generate force against the dynamometer for 2 seconds, and then maintains a maximal effort for another 5 seconds. For elbow flexion, the dynamometer is positioned in the participant’s hand, with the participant pressing the device upwards, onto the underside of the table. For elbow extension, the dynamometer placed in the participant’s hand, with the participant pressing the device downwards, onto the topside of the table. For elbow extension, the dynamometer placed proximal to wrist on extensor surface of forearm, with the participant pressing downwards, into the dynamometer. The participant will complete two trials per arm with the maximum value per arm recorded to the nearest kilogram. Waist circumference (WC) will be measured according to the World Health Organization protocol, with measuring tape positioned at the midpoint between lowest rib and iliac crest Body mass index (BMI, kg/m^2^) will be calculated using the participant’s height (m) and weight (kg). Body fat percentage will be measured through bioelectrical impedance analysis (Tanita Corporation, model TBF-300A, Tokyo, Japan). Aerobic fitness will be measured using the 6-Minute Walk Test (6MWT) [40] that involves the participant walking a 15 meter linear course for 6 minutes (turning around at each end) with the total distance traveled recorded. Motivational and time-remaining cues are standardized to the following:

1:00 – “You’re doing well. You have 5 minutes to go”.

2:00 – “Keep up the good work. You have 4 minutes to go”.

3:00 – “You’re doing well. You’re halfway done”.

4:00 – “Keep you the good work. You have 2 minutes left”.

5:00 – “You’re doing well. You have only 1 minute to go”.

5:45 – “In a moment I’m going to tell you to stop. When I do, just stop right where you are and I will come to you”.

PCa-specific HRQOL will be measured using the psychometrically validated Functional Assessment of Cancer Therapy-Prostate (FACT-P) [41] and the Patient-Oriented Prostate Utility Scale (PORPUS) [42]. Anxiety and depression will be measured by the Hospital Anxiety and Depression Scale (HADS) [43]. The HADS demonstrates strong construct validity and is sensitive to a counseling intervention [44, 45]. Cancer-specific fatigue will be measured using the Functional Assessment of Cancer Therapy-Fatigue (FACT–F) which is a widely used 13-item measure with strong reliability and validity [45, 46]. The Pain Disability Index (PDI) [47] will be used to assess the extent to which persistent pain interferes with an individual’s ability to engage in activities of daily living [48]. Urological symptoms are assessed using the valid and reliable, 7-item International Prostate Symptom Score (IPSS) [49, 50]. Erectile function is assessed using the 5-item International Index of Erectile Function (IIEF) scale, a widely used, psychometrically validated multi-dimensional self-report instrument evaluating male sexual function [51, 52].

Physical activity level will be measured at each time point through the Community Health Activities Model Program for Seniors (CHAMPS) questionnaire [53]. The CHAMPS is a self-reported measure of physical activity, comprising 41 activities evaluated according to the total number of hours done during an average week that can be translated into average weekly caloric expenditure. Acute postoperative physical activity will also be objectively measured via accelerometer from postoperative admission to the inpatient ward until the participant returns to the ambulatory clinic for catheter removal (typically 1–2 weeks). The Actiwatch 2 (Philips Healthcare, Respironics, PA, USA) is a light-weight accelerometer worn as a wristwatch on the non-dominant arm that is water resistant and can be worn during bathing. The Actiwatch 2 can reliably measure movement volume in three dimensions and quantified using the unit of ‘activity counts’ (AC) over multiple days [54–56]. ACs (in counts per minute; cpm) will be captured and stratified into the following categories for analysis: sedentary (0–99 cpm), light activity (100–1951 cpm), and moderate-to-vigorous activity (>1951 cpm). As reported by Lynch et al. [57], physical activity volume will be analyzed using percentage of device-wearing time (in minutes) spent in the various activity categories.

Treatment complications and length of stay data will be extracted from medical records.

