### Statistical analysis

Participant characteristics will be summarized using descriptive statistics (mean, standard deviation, frequency). The equivalence of groups at baseline in terms of demographic and clinical variables will be assessed using independent samples t-tests for continuous variables and chi-square tests for categorical variables. We will report recruitment and attrition rates per site with comparison between sites using the chi-square test. Adherence to the PREHAB and PFMX prescriptions will be compared across study sites using independent samples t-tests. Estimates of efficacy (Group and Time main effect, as well as Group x Time interactions) will be analyzed using a repeated-measure analysis of covariance (ANCOVA), controlling for the baseline value of the outcome of interest and study site. Frequency of perioperative complications will be compared between the PREHAB and UC groups using chi-square analysis and as per the Clavien-Dindo classification system [58]. Length of stay between the PREHAB and UC groups will be compared using independent samples t-test.

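### The repetition-based adherence formula cannot score the aerobic part of the PREHAB programme, which is prescribed in minutes

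*Protocol article*

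**What the plan says.** All references are to the protocol article.

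- **Status of the outcome.** Methods/Design makes feasibility of a full-scale trial the primary objective. Outcome assessments lists adherence among the measures of feasibility, beside recruitment, attrition and contamination.
- **What is scored.** Outcome assessments applies one metric to "Adherence to the exercise prescription for the PREHAB intervention and to the PFMX prescription for both groups". The metric is obtained by "calculating the percentage of total physical activity volume prescribed", and a parenthesis then defines it: "i.e. total number of repetitions completed/total number of repetitions prescribed".
- **What is prescribed.** Under PREHAB, a session lasts 60 minutes and is done on 3–4 days per week. Its aerobic part is given by time and intensity: "25 minutes of aerobic exercise (40-60% of heart rate reserve; HRR"). Its resistance part is as long and is the only one of the four parts described in repetitions: five exercises at 8–12 repetitions maximum. Warming up and cooling down take 5 minutes each. PFMX is prescribed as a daily number of repetitions.
- **How it is analysed.** Statistical analysis states: "Adherence to the PREHAB and PFMX prescriptions will be compared across study sites using independent samples t-tests".

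**The concern.** The metric and the prescription use different units. A ratio of repetitions suits PFMX and can be made to work for resistance training. The aerobic block is set by time and heart-rate reserve, so there is nothing to count in repetitions.

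Followed as written, the formula scores the exercise prescription on resistance work alone. The programme is done at home and unsupervised, so whether men complete it is one of the main things this pilot has to find out. If men keep up one component better than the other, the reported percentage will not show it, and a decision on the full-scale trial could rest on that percentage.

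**Working it through.** **Inputs** (all from PREHAB, except the preoperative wait of typically 4–8 weeks, from Study arms): warm-up 5 min, aerobic 25 min, resistance 25 min, cool-down 5 min; 3–4 days per week; 5 resistance exercises at 8–12 repetitions maximum, with no number of sets given.

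**1. Reproduce the stated session length.** 5 + 25 + 25 + 5 = 60 min, as stated.

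**2. Share of the session that the ratio does not see.**
- Aerobic share of training time: 25 / (25 + 25) = 50%.
- Aerobic share of the whole session: 25 / 60 = 42%.
- All time without a repetition count, including warm-up and cool-down: 35 / 60 = 58%.

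**3. Effect on the score.** Let *a* and *r* be the fractions of prescribed aerobic and resistance work completed.
- Stated formula: score = *r*; *a* does not appear.
- By training time: score = (25*a* + 25*r*) / 50 = (*a* + *r*) / 2.
- Difference: *r* − (*a* + *r*) / 2 = (*r* − *a*) / 2.

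With all resistance and no aerobic work (*r* = 1, *a* = 0), the stated score is 100% and the time-based score 50% (35/60 = 58% if warm-up and cool-down are counted as done). With the reverse (*r* = 0, *a* = 1), the stated score is 0% and the time-based score 50%. The formula therefore overstates adherence when resistance work is kept up better than aerobic work, and understates it in the opposite case. The error is at most 50 percentage points.

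**4. Size of the unscored prescription.** 25 min × 3 days × 4 weeks = 300 min, up to 25 × 4 × 8 = 800 min per man.

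**5. Denominator for what is scored.** The frequency is a range. Three full sessions a week give 3/3 = 100% against the lower end and 3/4 = 75% against the upper end. Fixing the denominator at three days does not solve this, because a man doing the permitted four days would score 4/3 = 133%. With the repetition range added, the resistance denominator varies by (4 × 12) / (3 × 8) = 2.0 for any given number of sets.

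**The case against.** The best defence is that the governing phrase, "calculating the percentage of total physical activity volume prescribed", is wide enough to include minutes, and that the parenthesis was meant as an example for PFMX, with i.e. written for e.g. That may well be so. The text in force nevertheless defines the metric by repetitions and applies it to the whole exercise prescription, so it needs correcting even if it is a slip. The weekly log is not shown and may already record aerobic minutes; in that case only the definition has to change.

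On the denominator, sessions are individualized from a baseline assessment, so each man may have his own recorded target. That is a fair answer, and the fix below uses it.

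A reader might infer more than the document supports:

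- **That the ratio is also meant to measure contamination, and fails because usual care has no exercise prescription.** The ratio is applied only to adherence. Contamination is assigned to the physical activity log kept at the weekly contact.
- **That contamination has no estimate.** The log is its named source, and the CHAMPS activity questionnaire is collected in both arms at every time point. The usual-care contact is described as "weekly communication from the RC regarding compliance with the PFMX prescription to provide an attentional-control", which leaves some doubt whether the log asks those men about other exercise. It does not say that the contact is confined to PFMX, and an article may leave the contamination metric to the full protocol or SAP.
- **That PFMX and resistance repetitions are added together, so that PFMX dominates.** Outcome assessments and Statistical analysis both name the two prescriptions separately, and PFMX needs its own score in usual care. Any figure for a pooled score would rest on an unstated reading and an assumed number of sets.
- **That comparing adherence by site rather than by arm is an error.** A site comparison is reasonable in a two-centre pilot, and nothing precludes a by-arm summary.

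**Conclusion.** The point holds for the aerobic component. As written, the adherence formula in Outcome assessments does not fit the prescription under PREHAB, and it leaves out 50% of training time (42% of the session). A man who does no aerobic exercise can score 100%, against 50% by training time.

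The 50% comparison assumes that aerobic and resistance minutes carry equal weight and that the fraction of repetitions done equals the fraction of resistance time done. That the aerobic work goes unscored needs neither assumption. How far the trial's reported figure would be off depends on the gap between aerobic and resistance completion, which the document cannot tell us.

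The problem is limited to adherence to the PREHAB exercise prescription. PFMX adherence is scored in its proper unit, and recruitment and attrition do not use the formula.

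**What to change.** Replace the single repetition ratio with three scores, reported separately and not summed:

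1. aerobic: minutes (or sessions) completed / prescribed;
2. resistance: sets or repetitions completed / prescribed;
3. PFMX: repetitions completed / prescribed.

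Take the aerobic and resistance denominators from each participant's own recorded prescription over his actual weeks to surgery, so that the 3–4 day range does not leave the score open. Confirm that the weekly log records aerobic minutes. This should be settled before data collection, since aerobic minutes not asked for at the weekly contact may be hard to reconstruct later.

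The cost is small: a revised definition, an aerobic field in the log if it lacks one, and a few more lines of analysis. The drawback is that adherence becomes three figures instead of one.

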### Statistical analysis

Participant characteristics will be summarized using descriptive statistics (mean, standard deviation, frequency). The equivalence of groups at baseline in terms of demographic and clinical variables will be assessed using independent samples t-tests for continuous variables and chi-square tests for categorical variables. We will report recruitment and attrition rates per site with comparison between sites using the chi-square test. Adherence to the PREHAB and PFMX prescriptions will be compared across study sites using independent samples t-tests. Estimates of efficacy (Group and Time main effect, as well as Group x Time interactions) will be analyzed using a repeated-measure analysis of covariance (ANCOVA), controlling for the baseline value of the outcome of interest and study site. Frequency of perioperative complications will be compared between the PREHAB and UC groups using chi-square analysis and as per the Clavien-Dindo classification system [58]. Length of stay between the PREHAB and UC groups will be compared using independent samples t-test.

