To enhance the overall surgical experience for patients, an important question revolves around *when* the most opportune time is to introduce recovery-optimizing behaviours. The postoperative period may be less than ideal due to concerns related to perturbing the healing process as patients await additional results or treatments. Instead, an emerging field of research describes the role of preoperative strategies to improve treatment tolerance and recovery. The preoperative period may be more physically and emotionally salient for patients by capitalizing on: i) the generally better physical condition of the patient (compared to the acute postoperative period), ii) surgical wait-list times, and iii) a ‘teachable moment’ for the patient that accompanies the need for major surgery [14]. Ultimately, it appears that the preoperative period may be an optimal time to invest into the modifiable factors that contribute to peri- and postoperative health.

A health behaviour that has demonstrated great promise in terms of its beneficial relationship with perioperative complications and postoperative recovery is physical activity and the consequential improved physical fitness levels. Studies routinely report that patients who are physically active and fit recover more quickly, have fewer perioperative complications, and experience better convalescence compared with patients who are less physically active and fit [15–21]. *Pre*-habilitation is defined as the process of enhancing one’s functional and mental capacity to enable him/her to withstand a significant stressor [22]. In a surgical setting, preoperative physical and/or psychological conditioning aims to increase body and mind reserves to prevent the declines in postoperative wellbeing [22]. Recently published systematic reviews of prehabilitation have described numerous benefits to postoperative wellbeing across a variety of surgical populations [23–25], including cancer-patients specifically [26]. Carli and colleagues have shown that prehabilitation can improve postoperative physical function in cancer patients undergoing colorectal surgery [27, 28], hysterectomy [29], and lung resection [30]. Their group has also found that improvements in physical function were associated with improvements in mental health, vitality, and self-perceived health [31]. Moreover, it appears that control subjects whose fitness deteriorated preoperatively had more surgical complications and greater need for intensive care [31].

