### Study recruitment and randomization

Eligible patients will be recruited from ambulatory urology clinics at each site by a research coordinator (RC). Recruitment posters will also be placed in hospital waiting areas. Written informed consent will be collected from all patients prior to participation.

Participants will be randomly allocated to either the PREHAB or UC groups prior to the baseline assessment, stratified by study site. Blinded allocation of participants to their treatment groups will be performed via sequentially numbered opaque envelopes that will contain intervention assignments that have been shuffled to create a random order. Figure 1 provides the structure of participant flow through each intervention arm.

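### Length of stay and complications are compared without a covariate although baseline fitness and site are at hand: the tests are valid, but some precision is given up

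*Protocol article*

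**What the plan says.** All references are to the Protocol article.

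- **Length of stay** (Statistical analysis): "Length of stay between the PREHAB and UC groups will be compared using independent samples t-test".
- **Complications** (same section): "Frequency of perioperative complications will be compared between the PREHAB and UC groups using chi-square analysis", with Clavien-Dindo grading. Neither comparison has a covariate or a site term.
- **Repeated outcomes** (same section): a repeated-measures ANCOVA, "controlling for the baseline value of the outcome of interest and study site".
- **Role of fitness** (Background): studies are said to show that "patients who are physically active and fit recover more quickly, have fewer perioperative complications, and experience better convalescence". A further sentence reports that "control subjects whose fitness deteriorated preoperatively had more surgical complications and greater need for intensive care".
- **Baseline measurement** (Outcome assessments): "Self-report measures and physical fitness assessments will be conducted at: baseline (following RP booking, prior to beginning group assignment". The fitness battery includes the 6MWT as the aerobic measure, plus grip and elbow strength.
- **Order of randomization** (Study recruitment and randomization): "Participants will be randomly allocated to either the PREHAB or UC groups prior to the baseline assessment, stratified by study site".
- **Purpose** (Methods/Design and Discussion): feasibility is primary and efficacy estimates are secondary. The effect sizes are meant to inform the sample size of later trials.

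**The concern.** The plan adjusts the repeated outcomes for a prognostic variable, namely their own baseline value. Length of stay and complications have no baseline value, and nothing replaces it. Yet the Background argues that fitter men have fewer complications and recover faster, and the trial measures fitness before surgery. Site is the stratification factor and is already in the ANCOVA, but it is also left out of these two comparisons.

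If baseline fitness is prognostic, two things follow. Variance that could be explained stays in the error term, so the interval is wider than it need be. And if one arm happens to be fitter, that difference carries into the observed contrast. The article tests baseline balance but states no consequence if the arms differ. A covariate fixed in advance settles that before any data are seen. Because the estimates will feed later sample-size planning, their precision is what counts here.

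**Working it through.** **1. The plan's own figure.** The sample size is 100, with 50 per group: 2 × 50 = 100. With the anticipated 20% attrition, 100 × 0.8 = 80, or 40 per arm. The article justifies 100 by pilot-study convention and states no effect size, SD, event rate or power, so there is no power figure to reproduce. Length of stay and complications come from medical records, so 40 per arm is probably a pessimistic case for them.

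**2. Inputs that must be assumed.** The documents give no correlation r between baseline 6MWT and length of stay; I take 0.1 to 0.4. Differences are in SDs of length of stay. Power uses an assumed difference of 0.5 SD and two-sided α of 0.05.

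**3. Precision for length of stay.** The unadjusted SE is √(2/n): 0.200 SD at 50 per arm, 0.224 SD at 40. Adjusting for one covariate multiplies the variance by (1 − r²) × (1 + 1/(2n − 4)). The second factor is the price of estimating the covariate: 1 + 1/96 = 1.0104 at 50 per arm and 1 + 1/76 = 1.0132 at 40. Equivalent extra men = 1/ratio − 1.

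| r | Variance ratio, 50/arm | Extra men, 50/arm | Extra men, 40/arm | Power, 50/arm (unadjusted 70.5%) |
|---|---|---|---|---|
| 0.1 | 1.00 | 0% | −0.3% | 70.5% |
| 0.2 | 0.97 | 3% | 3% | 71.9% |
| 0.3 | 0.92 | 9% | 9% | 74.1% |
| 0.4 | 0.85 | 18% | 18% | 77.4% |

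**4. Chance imbalance.** The difference in mean baseline fitness between arms has SD √(2/50) = 0.20 of a fitness SD. Its contribution to the unadjusted length-of-stay difference therefore has SD 0.20r: 0.02, 0.04, 0.06 or 0.08 SD. At the edge of its 95% range (1.96 × 0.20 = 0.39) the shift is 0.39r: 0.04, 0.08, 0.12 or 0.16 SD. The unadjusted 95% half-width is also 0.39 SD, so it already allows for these shifts.

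**5. Validity.** In simulation (8,000 runs per setting, normal outcomes, r of 0.3 and 0.5, 40 and 50 per arm) the unadjusted t-test had type I error of 4.6% to 5.0%. Its mean estimate was 0.50 to 0.51 for a true 0.50. There is no bias and no loss of level. With r = 0.3 and 50 per arm, the empirical SE fell from about 0.20 to about 0.19 with adjustment.

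**6. Site.** If the two site means differ by D within-site SDs, site explains R² = (D²/4)/(1 + D²/4) of the variance, and the t-test's SE is inflated by 1/√(1 − R²). For D = 0.25, 0.5 and 1.0, R² is 0.015, 0.059 and 0.20, and the inflation is about 1%, 3% and 12%. With arms balanced within site, this errs towards caution.

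**7. Complications.** At an assumed overall risk of 20% (20 events in 100 men), an odds ratio of 1.35, 1.65 or 2.23 per SD of fitness explains 1.4%, 3.8% or 9.2% of the outcome variance. The possible gain is small over most of that range.

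**The case against.** The strongest reply is that nothing is wrong with the stated tests. Randomization makes the unadjusted contrast unbiased, its interval already covers chance imbalance in fitness, and adjustment is only an efficiency option whose size is entirely assumed. Adjusting the repeated outcomes for their own baseline does not oblige the authors to find a substitute where none exists. All of that stands, and it limits the point to precision and to imbalance in the realised sample.

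Stronger readings are tempting, but the article does not support them:

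- **That the protocol says fitness predicts both outcomes.** It names complications and speed of recovery. Length of stay is never tied to fitness; the link is an inference from quicker recovery. The sentence on deteriorating fitness concerns change before surgery among controls, not baseline level.
- **That the protocol names the 6MWT as the prognostic variable.** It speaks of active and fit patients. Strength or questionnaire-reported activity could also serve; the 6MWT is a reasonable choice, not a stated one.
- **That these are the only outcomes without a baseline value of their own.** Accelerometer activity is also recorded only after surgery.
- **That omitting the covariate biases the result or invalidates the test.** Step 5 shows otherwise.

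It can also be said that covariates for secondary comparisons are often left to an analysis plan. Here, however, the article fixes both tests by name, so this is a stated choice and not an omission.

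**Conclusion.** The point holds as a modest matter of efficiency. Two comparisons are fixed without covariates, although the same section adjusts the repeated outcomes for baseline and site, the Background gives a reason to expect fitness to be prognostic for complications and recovery, and fitness is already collected.

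For length of stay at 50 per arm, the net gain from adjusting for the 6MWT is about 0%, 3%, 9% or 18% more men for r of 0.1, 0.2, 0.3 or 0.4. It is negligible to small up to r = 0.2 and worth having from about 0.3. Every one of these figures rests on an assumed correlation. For complications the gain is small and depends on the number of events. The site term is the better-documented inconsistency, since site is both the stratification factor and an ANCOVA covariate.

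Priority is low: efficacy is secondary in a feasibility pilot, and the planned tests are valid as they stand.

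**What to change.** 1. **Length of stay.** Replace the t-test with a pre-specified linear regression of length of stay on arm, baseline 6MWT distance and study site. Report the adjusted mean difference with a 95% confidence interval from robust standard errors.
2. **Complications (optional).** If there are enough events, report the risk difference for any complication, standardised over the same covariates. Otherwise keep the unadjusted comparison.
3. **Order of procedures.** Reconcile the randomization section, which allocates men before the baseline assessment, with Outcome assessments, which puts baseline before group assignment begins. The second wording may mean only before the assigned programme starts. The 6MWT depends on effort, so it is a safe covariate only if it is done before the allocation envelope is opened.
4. **Missing baseline 6MWT.** State a simple imputation that ignores arm, such as the overall mean, so that no man is dropped.

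Cost: a few sentences of text, one or two degrees of freedom, the imputation rule, and possibly a small change in the order of the baseline visit and the opening of the envelope. No new measurement is needed.
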